### Statistical analysis

2.11

The analysis will be described for all results included in the study. Quantitative outcomes will be expressed with their mean ± standard deviation, and qualitative results will be described with their absolute value, percentage, and 95% confidence intervals.

Data will be analyzed using SPSS V.22.0 software. To observe the associations between the qualitative variables, *χ*2 test will be used. Before comparing the means, Kolmogorov–Smirnov test and the Levene test will be used to confirm the normal distribution and homogeneity of the variances of the quantitative variables. For variables with normal distribution, Student t-test will be used; for variables with a non-normal distribution, Mann–Whitney test will be used. Analysis of variance mixed model will be used to estimate of the average effect (differences between groups) for all variables. This analysis model incorporated the groups (intervention and control group), time (baseline, 2 weeks and 6 weeks), and the group × time interaction. When a significant *F* value is found, the Bonferroni post-hoc test will be applied to identify the differences. The size of the effect between the groups for the variables that present intergroup differences can be calculated at some point, with 95% confidence intervals. The level of statistical significance adopted will be 5%. The analysis will be performed by an independent researcher.

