**Methods and analysis::**

This is a protocol proposal for a prospective, single-center, randomized, controlled study. We plan to recruit adults discharged after ACL reconstruction; the recruited subjects will be randomly allocated to 1 of 2 groups, using a computer-generated randomization method: the intervention (n = 20) or control group (n = 20). The intervention group will receive a 6-week home-based rehabilitation program using smart wearable device. The control group will undergo a 6-week self-exercise program as normal. The following outcomes will be assessed at baseline, 2 weeks, and 6 weeks post the 6-week intervention program: quadriceps strength of the affect side as measured by a dynamometer (primary outcome); range of motion; root mean square of quadriceps muscle using surface electromyography; knee function using questionnaire; quality of life; subject's satisfaction score using questionnaire; frequency and duration of exercise; and knee pain. An intention-to-treat analysis will be conducted for the primary outcome.

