#### Sample size calculation

2.10.1

This study was designed as an exploratory trial with 2 groups – intervention and control groups – using a dynamometer. The sample size calculation was based on the difference in the quadriceps strength (torque, Nm) between the 2 groups from the baseline to the 6-week follow-up. The following formula was used to calculate the number of participants needed in each group:
 
[figure not shown]

According to a previous study, the difference in the means of 6-week quadriceps strength was 33, with a standard deviation of 30.^[27]^ Based on the 5% 2-sided significance level and 80% power, at least 14 participants are needed in each group. With an attrition rate of 30%, our study will recruit a total of 20 participants in each group.

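### The mixed ANOVA named in section 2.11, read in its usual form, analyses only participants with all three visits, which fits poorly with the promised intention-to-treat analysis when 30% attrition is planned

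*Protocol article*

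**What the plan says.** Three parts of the protocol article bear on this.

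- **Analysis model (2.11 Statistical analysis).** "Analysis of variance mixed model will be used to estimate of the average effect (differences between groups) for all variables". The terms are group, "time (baseline, 2 weeks and 6 weeks), and the group × time interaction". A significant F value leads to Bonferroni post-hoc tests. Student t or Mann-Whitney tests stand beside the model, with Kolmogorov-Smirnov and Levene checks beforehand. On software the section says "Data will be analyzed using SPSS V.22.0 software" and names no procedure within it.
- **Analysis population (Abstract, Methods and analysis).** "An intention-to-treat analysis will be conducted for the primary outcome". Section 2.11 does not repeat or define this.
- **Expected loss (2.10.1 Sample size calculation).** "Based on the 5% 2-sided significance level and 80% power, at least 14 participants are needed in each group", and then "With an attrition rate of 30%, our study will recruit a total of 20 participants in each group".

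**The concern.** The wording of 2.11 points towards a classical between-within ANOVA. Baseline is a level of the time factor, an F test acts as gatekeeper for post-hoc comparisons, and the checks are those of the t-test family. No covariance structure, random effect or estimation method is mentioned. In its usual repeated-measures form that procedure needs a complete row for each participant. Someone measured at baseline and week 2 but not at week 6 contributes nothing, and the accompanying week-6 t-test leaves the same person out.

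The analysed groups would then be the completers rather than the groups as randomised. Two things are at stake. First, data already collected from leavers would go unused. Second, if the reasons for leaving differ between arms, the completer comparison is biased. A difference between arms is plausible here, because only the device arm receives electrical stimulation (2.5.2 and 2.5.3), and 2.7 provides for withdrawal from the study because of discomfort.

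**Working it through.** **1. The plan's own figures.** Inputs from 2.10.1: difference 33, SD 30, two-sided 5%, 80% power, 30% attrition.

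- Normal approximation: n = 2 × [30 × (1.960 + 0.842) / 33]² = 12.97, so 13 per arm.
- Solved with the t distribution: 14.00 per arm, with 80.0% power at 14.
- Attrition: 14 / (1 − 0.30) = 20 per arm.

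Both stated figures, 14 and 20, reproduce. Power is planned on 14 evaluable participants per arm, which is in line with a completer analysis but does not prove that one is intended.

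**2. How many would drop out of the analysis.** 0.30 × 20 = 6 per arm, or 12 of the 40 randomised. The article does not say when they leave, so the number who would have a week-2 value is unknown.

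**3. Bias in the completer comparison.** The documents give no covariance between visits and no dropout mechanism, so the following are assumptions: SDs 20/25/30 Nm at baseline/2/6 weeks, correlations between visits of 0.4-0.7 or 0.5-0.8, and 20 per arm with 30% lost after week 2. Where leaving is selective, it follows a logistic relation to week-2 strength with slope 1 or 2 per SD; otherwise it is random. Simulated results for completers:

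| Leaving related to week-2 strength in | Bias, change from baseline | Bias, raw week-6 difference | False positives, change | False positives, raw |
|---|---|---|---|---|
| both arms alike | about 0 | about 0 | about 5% | about 5% |
| device arm only | about +3 to +5 Nm | about +5 to +9 Nm | about 6-7% | about 7-12% |
| control arm only | mirror image (negative) | mirror image (negative) | about 6-7% | about 7-12% |

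The signs assume that weaker patients are the ones who leave. Against the planned difference of 33 Nm, the change bias is 3/33 = 9% to 5/33 = 15%, and the raw bias is 5/33 = 15% to 9/33 = 27%. The change figures are the more relevant ones, because 2.10.1 sizes the trial on baseline to 6 weeks and the group × time term tests change.

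**4. A second set of assumptions.** Here the SD is 30 at every visit, the within-person correlation 0.5 or 0.7, the true difference 33 Nm (16.5 Nm at week 2), and leaving depends on change by week 2, with about 25% to 37% lost. Mean completer difference in change:

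- random leaving: 33.0
- poor progress drives leaving in both arms: 31.7 to 32.0
- in control only: 28.8 to 30.1
- in intervention only: 34.9 to 36.4
- opposite directions in the two arms: 37.1 to 39.9

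The range of bias is therefore about −4 to +7 Nm.

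**5. Using all collected visits.** A likelihood-type estimate (sequential regressions of week 6 on baseline and week 2, fitted by arm) gave 32.8 to 33.4 Nm throughout step 4, and was within a few tenths of a Nm of the truth in step 3. This is expected, because leaving was made to depend only on observed values.

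**6. Secondary point.** The univariate time and group × time F tests assume sphericity, which the Kolmogorov-Smirnov and Levene checks do not address. Under assumed covariances (epsilon 0.57 to 0.86) the uncorrected interaction test rejected in 5.4% to 7.9% of null trials, against 4.4% to 5.3% with the Greenhouse-Geisser correction.

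**The case against.** The strongest reply is that the article never says incomplete participants are dropped. The model name can also be read as a linear mixed model, which the same software offers, which keeps partial data, and which also yields F tests and Bonferroni comparisons. This is a condensed article, and rules for missing visits may sit in a fuller document. That stands. The incompatibility with intention-to-treat holds only on the classical reading, and a missing imputation rule is not the complaint. What remains is that the method named here, in its ordinary meaning, does not suit the promised analysis, and a better one in the same software can be named.

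Several stronger readings are tempting, and the documents do not support them:

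- *Any dependence of leaving on early progress biases the result.* It does not. When both arms behave alike the bias is near 0 (about −1 Nm in the second set of assumptions).
- *The bias favours the device.* Selective leaving in the control arm gives the opposite sign, and nothing in the article fixes which arm loses its weaker patients.
- *Week-2 data exist for all of the 30%.* No timing of attrition is given.
- *Power falls below 80%.* The 14 per arm already allows for the 30% loss, further missed visits are not mentioned anywhere, and a week-6 t-test needs no earlier visit.

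It is also fair to say that section 2.6, which exempts withdrawn participants from follow-up assessments, is a firmer obstacle to intention-to-treat. That is a separate matter, and a change of model does not cure it.

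**Conclusion.** The point holds as a conditional one. On the usual repeated-measures reading, the analysis in 2.11 is a completer analysis and fits poorly with the abstract's promise when 12 of 40 participants are expected to be lost. A reader might infer a stated completers-only rule, and so an outright contradiction; the text contains no such rule.

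The consequence ranges from nothing, if leaving works alike in both arms, to about 3 to 5 Nm in change from baseline if it is selective in one arm only, with a false-positive rate of about 6-7%. The raw week-6 comparison fares worse. Mechanisms running in opposite directions could add to this.

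These sizes rest on assumed SDs, correlations and dropout after week 2. They illustrate rather than forecast, also because 2.6.1 reports the primary outcome as a side-to-side percentage and not in Nm. The change is worth making because it is cheap and, with data collection still under way at submission (2.2), can precede the final analysis.

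**What to change.** In 2.11, replace the ANOVA wording with a named model:

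- a linear mixed model fitted by REML (SPSS MIXED), with the 2- and 6-week values as response;
- baseline value, group, visit and group × visit as fixed effects, and an unstructured covariance between visits;
- every randomised participant with at least one post-baseline value included, in the group to which they were randomised;
- the week-6 group contrast with its 95% confidence interval as the primary estimate.

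If an ANOVA is kept, label it a completer sensitivity analysis and report Greenhouse-Geisser corrected F tests.

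The cost is a paragraph of text and a different procedure in the software already chosen; no new data are needed. There are two limits. The model removes the bias only if loss depends on observed values, so leaving for unrecorded reasons linked to later strength would still distort the result. Participants with no post-baseline value still contribute nothing, so their number should be reported by arm.

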### Patient and public involvement

2.12

Patients or the public were not involved in the design of this study. Informed consent and all study information will be given to all participants. Only after willingly consenting and understanding of the study, patients will be randomized. The results of the assessment can be released to participants on request.

### Ethics and dissemination

2.13

This protocol has been approved by the IRB of the Seoul National University Bundang Hospital (IRB No. B-1806-475-006). The trial will be conducted in accordance with the International Conference on Harmonisation Good Clinical Practice. All study procedures will adhere to the Declaration of Helsinki. The primary results will be submitted for publication to an international, peer-reviewed journal, regardless of whether the results are positive, negative, or inconclusive with respect to the study hypothesis. Authorship eligibility will be based on the recommendations from the International Committee of Medical Journal Editors. Any important protocol amendments will be reported to the IRB of the Seoul National University Bundang Hospital and registered at ClinicalTrials.gov.

## Discussion

3

This study aims to investigate the feasibility and efficacy of a 6-week, structured home-based rehabilitation program for patients after ACL reconstruction using smart wearable device, which is an all-in-one home-based rehabilitation platform (range of motion exercise, strengthening using EMG biofeedback, electrical stimulation). This study is a prospective, single-center, randomized, controlled study. Subjects will be randomly allocated to 1 of 2 groups, the intervention (n = 20) or control group (n = 20). The following outcomes will be assessed at baseline, 2 weeks, and 6 weeks post the 6-week intervention program: quadriceps strength of the affect side as measured by a dynamometer (primary outcome); range of motion; root mean square of quadriceps muscle using surface EMG; knee function and subject's satisfaction score using questionnaire; quality of life; frequency and duration of exercise; and knee pain. It is hypothesized that patients receiving this rehabilitation program with device will show superior improvement in quadriceps muscle strength.
